## Abstract

**Background:**

The effectiveness of nonpharmacological interventions in blood pressure reduction has been evidenced by several studies. Nevertheless, as adherence to a low-sodium diet is poor, interventions regarding habit changing should be of a motivational nature in order to develop the ability of overcoming obstacles regarding sodium-restriction behavior.

The present study aims to describe the protocol and randomization of a clinical trial design in order to evaluate the effectiveness of an educational intervention based on Dietary Sodium Restriction Questionnaire (DSRQ) scores. The effectiveness measures are the DSRQ score variation and reduction in urinary sodium values from baseline to after 2 and 6 months.

**Methods/design:**

This parallel, randomized clinical trial will include 120 participants, recruited and randomized as follows: 60 of them to be allocated to a sodium-restriction educational intervention group whose results are based on the DSRQ application; and the other 60 allocated to a control group with usual care. Educational orientation and usual care sessions will be conducted once a month for a period of 6 months. Both spot urine collection – estimating sodium intake – and the DSRQ will be applied at the baseline, in the eighth week and at the end of the follow-up. There will also be blood collection and 24-h ambulatory blood pressure monitoring (ABPM) at the beginning and end of the follow-up. Anthropometric measurements, blood pressure measurement and 24-h food recall will be collected during follow-up.

**Discussion:**

The study “The effectiveness of an educational intervention to sodium restriction in patients with hypertension” is based on the results of the DSRQ application, whose objective is to evaluate aspects related to nonadherence to the recommendation of a low-sodium diet, identifying adherence barriers and facilitators, contributing to the planning of interventions for improving the adoption of a low-sodium diet and, consequently, hypertension control.

**Trial registration number:**

ClinicalTrials.gov, Identifier: NCT02848690. Registered retrospectively on 27 July 2016.

**Electronic supplementary material:**

The online version of this article (doi:10.1186/s13063-017-2091-4) contains supplementary material, which is available to authorized users.

## Background

Clinic trials have demonstrated the efficacy of nutritional interventions in the reduction of blood pressure [1–6]. According to a meta-analysis, sodium-intake restriction has shown effectiveness in reducing blood pressure in hypertensive and normotensive individuals [7]. Even salt-restriction diets, such as DASH (Dietary Approaches to Stop Hypertension) [1, 2] and the Mediterranean diet [6], were associated with a decrease in blood pressure levels. The guidelines to reduce salt intake to 5–6 g/day should, therefore, have a major effect on blood pressure, but a further reduction to 3 g/day will have an even greater effect and should become the long-term target for population salt intake [7].

In contrast, evidence has demonstrated that there is an increased risk of cardiovascular disease events and deaths associated with 24-h urinary sodium excretion of less than 3 g/day in both hypertensive and normotensive individuals. However, high-sodium intake (greater than 6 g/day) was associated with an increased risk in individuals with hypertension. These data suggest that lowering sodium intake is best targeted at populations with hypertension who consume high-sodium diets [8]. Thus, current evidence suggests a recommendation for moderate sodium intake in the general population (3–5 g/day), targeting the lower end of the moderate range among those with hypertension [9].

According to hypertension treatment guidelines, a daily intake of approximately 3.7 g/day (1500 mg of sodium) is recommended [10, 11]. Furthermore, a reduction of 2.0–4.6 g/day of salt can result in clinically significant lower systolic blood pressure [7]. However, low-sodium diet adherence is poor, since most patients are asymptomatic and present difficulties in adopting and perceiving the benefits of reduced sodium intake, usually considering them too restrictive [12]. Also, there is no measure considered as “gold standard” for assessing treatment adherence, making the perception of nonadherence difficult for health professionals [13].

Interventions for behavior change should develop motivation to achieve goals such as reducing salt addition during meal preparation as well as the consumption of salty food; besides that, health professionals should consider the need to incorporate strategies to improve the necessary skills to overcome obstacles related to salt-intake-restriction behavior; thus, help transforming intention into action and strengthen such intentions by improving the perception of self-efficacy and habit change [14].

Only providing information about food to be avoided would not be enough to change this behavior, it is also necessary to help patients find out other kinds of food, replacing salty aliments with a healthier diet but with the same level of dietary pleasure [15]. Thus, a hedonic change to lower salt levels may be achieved by gradual exposure to food with low-salt content, resulting in a reduction of the salty taste threshold [16]. Furthermore, simple advising, though in clinical environments and administered in each visit, tends to show low efficiency; moreover, even in intensive counseling, only 20 to 40% of the participants in clinical trials of sodium restriction reduced their consumption to below the maximum recommended limit of 2300 mg/day (100 mmol/day) [3, 17, 18].

The Dietary Sodium Restriction Questionnaire (DSRQ) was developed due to the lack of instruments for measuring low-sodium diets among patients with heart failure (HF), in order to improve adherence to a low-sodium diet [19]. This questionnaire aims to help identify facilitators and barriers to adherence to a low-sodium diet, which is useful in clinical practice in order to guide the development of interventions for patient education and counseling [19].

Adherence to a lifestyle modification program, in order to modify health behavior, is very difficult because there are many barriers to behavioral change, such as knowledge about the disease, health beliefs, relationships with health professionals, as well as a variety of social and environmental factors, including financial difficulties, lack of transportation, and long periods of waiting in hospitals and clinics [20].

### Objective

This study aims to describe the protocol and randomization of the clinical trial design in order to evaluate the effectiveness of an educational intervention based on DSRQ scores. The effectiveness measures are DSRQ score variation and urinary reduction in sodium values from baseline and after 2 and 6 months.

### Hypothesis

Patients with hypertension who participate in the intervention group show low-sodium diet adherence, which decreases blood pressure values assessed by ABPM and sodium urine excretion values after 2 and 6 months in comparison to the control group.

## Methods/design

### Study design

This study is randomized, single-center, parallel clinical trial, with a follow-up period of 6 months. The hypertensive outpatients of Hospital de Clínicas de Porto Alegre (HCPA), will be recruited and then invited by telephone to participate in a study. After a baseline evaluation, the participants will be randomly allocated into two groups: (1) an educational intervention group and (2) a control group; and monitored monthly. The flow of the study design is presented in Fig. 1. The study timeline and schedule of enrollment, interventions and assessments (Standard Protocol Items: Recommendations for Interventional Trials (SPIRIT) figure) and the SPIRIT Checklist are provided as Fig. 2 and Additional file 1, respectively.

**Fig. 1 Fig1:**
[figure not shown]
General overview of study design

**Fig. 2 Fig2:**
[figure not shown]
Study timeline and schedule of enrollment, interventions and assessments

### Eligibility criteria

The study will include female and male individuals, aged from 40 to 80 years, who are in treatment and being monitored at the hypertensive outpatient department of HCPA. Participants must not have been monitored by a nutritionist or followed a nutritional orientation for more than 6 months.

Participants will be excluded from the study if they fit into one or more of the following criteria*:* pregnancy or lactation; gastrointestinal tract disease; inflammatory disease; chemotherapy treatment; diabetes diagnosis; incapacity to engage in an interview and/or to participate in the intervention program without the need of third-party involvement.

### Randomization, allocation and confidentiality

The first visit will consist of: (1) eligibility confirmation, (2) informed consent signature and (3) sociodemographic and clinic data collection. After this initial visit, patients will be allocated to a control group or an intervention group, according to a randomized code. An independent person not involved in this study will possess a list with the computer-generated randomization codes. Randomization sequence will be generated in blocks of 6, according to specific software, as further explained. Participants will be allocated to one of the two groups, using numbered envelopes, by simple random sampling determined by a randomization list.

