### Study variables and methods of assessment

The research team will be responsible for the triage and selection of eligible participants, and three members of the team will obtain the written informed consent signatures prior to entering the study. Researchers will not be blinded to participant intervention. The investigators will be trained to perform anthropometric standardization and BP measurements as well as the application of questionnaires. A laboratory technician will collect both spot urine and blood collection after 12-h fasting and the samples will be forwarded for analysis.

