### Potential biases

This study has some limitations. It is difficult to target a specific behavior concerning salt intake because salt can originate from several natural sources or be added to food during cooking or food processing. The instrument is self-reported, and self-reported behavior measurements can present a range of bias such as data credibility. The open-label design can introduce some potential for biases and the sample size limits the external validity.

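### Allocation is described as both blocked and simple; if the fixed block of 6 is the real scheme, up to a quarter of allocations could be deduced in advance

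*Protocol article*

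**What the plan says.** In the Protocol article, the section Randomization, allocation and confidentiality states: "Randomization sequence will be generated in blocks of 6, according to specific software, as further explained". The next sentence has participants allocated "using numbered envelopes, by simple random sampling determined by a randomization list". No later part of the article gives the announced explanation.

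On safeguards, the same section says: "An independent person not involved in this study will possess a list with the computer-generated randomization codes". It places allocation after a first visit that covers eligibility, consent, and sociodemographic and clinical data. Study design likewise puts allocation after a baseline evaluation.

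On the setting:
- Study design: "This study is randomized, single-center, parallel clinical trial, with a follow-up period of 6 months". Patients are invited by telephone.
- Abstract, Methods/design: "60 of them to be allocated to a sodium-restriction educational intervention group", with the other 60 in the control group.
- Study variables and methods of assessment: "The research team will be responsible for the triage and selection of eligible participants". Three team members obtain consent, and "Researchers will not be blinded to participant intervention".
- Potential biases: "The open-label design can introduce some potential for biases".
- Table 1, baseline row: spot urine and blood collection are listed after randomization.
- Trial status: recruitment began in November 2015.

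**The concern.** Two adjacent sentences name incompatible methods. Under simple randomization each allocation is independent of those before it. Under blocks of 6 the later allocations in a block depend on the earlier ones. A reader cannot tell which was used, and the two differ in how predictable they are.

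If blocking is the real scheme, the people who choose and consent patients can learn past allocations, and there is one centre with one stated block size. Someone keeping a tally could know the next arm before deciding whom to invite or when. The protocol leaves room for this: invitations go out by telephone, and one exclusion (being unable to take part in an interview or the programme without help) calls for judgement.

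At stake is selection bias. The intervention works through motivation, and the DSRQ score and urinary sodium are both primary outcomes. If more motivated patients were steered into one arm, both could shift in that arm's favour. Adjustment for baseline values may correct this only in part, because motivation itself is not fully measured.

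**Working it through.** **Inputs.** Block size 6, 1:1 allocation (60 and 60), one centre and a total of 120 all come from the Protocol article. No stratification is mentioned, so one running sequence is assumed. The article gives no predictability figure to reproduce. Its total of 120 agrees with 48 per group and a 20% loss allowance: 96 / (1 − 0.20) = 120.

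**Step 1: structure.** A 1:1 block of 6 holds 3 + 3 places, and 120 / 6 = 20 blocks. The number of possible orders per block is C(6,3) = 20.

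**Step 2: certain allocations.** An allocation is certain once one arm's three places are used. The last j allocations of a block are all certain with probability 2 × C(6 − j, 3) / 20:
- j = 1: 2 × 10 / 20 = 1.0
- j = 2: 2 × 4 / 20 = 0.4
- j = 3: 2 × 1 / 20 = 0.1

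Expected certain allocations per block: 1.0 + 0.4 + 0.1 = 1.5. The closed form 2m/(m + 1) with m = 3 gives 6/4 = 1.5 as well. As a share this is 1.5 / 6 = 25%, and over the trial 20 × 1.5 = 30 of 120.

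**Step 3: best guess.** Always guessing the arm with more places left gives, per block, m + 2^(2m−1)/C(2m,m) − 1/2 = 3 + 32/20 − 0.5 = 4.1 correct. That is 4.1 / 6 = 68.3%, or 20 × 4.1 = 82 of 120. Full enumeration of the 20 orders gives the same 1.5 and 4.1.

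**Step 4: if allocation is truly simple.** The certain share is 0% and the best-guess rate is 50% (60 of 120).

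**Step 5: effect of varying the block size.** The sizes below are an assumption, drawn with equal probability. For the varying sizes, 1,500 lists of 120 were simulated with a recruiter who knows the set of sizes but not their order.

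| Scheme | Certain | Best guess correct |
|---|---|---|
| Fixed 6 (exact) | 25.0% | 68.3% |
| 4 and 6, varied | 5.6% | 69.2% |
| 4, 6 and 8, varied | 2.4% | 67.9% |
| Simple | 0% | 50% |

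With 4, 6 and 8, certain allocations fall from 30 to about 3 of 120 (0.024 × 120 = 2.9). The best-guess rate hardly moves.

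**Step 6: stated safeguards.** Independent custody and numbered envelopes keep the list itself from view. The deduction in Step 2 needs only the block size and the past allocations, so these safeguards do not block it. Consent before allocation stops a change of mind after the envelope is opened, but not the timing or withholding of an invitation beforehand.

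**The case against.** The other side has several fair points.

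- **The 25% is a ceiling.** It needs a recruiter who knows the block size, learns every allocation in order and knows where each block starts. The article says the researchers are not blinded; it does not say that each of them follows the running sequence. With several patients between telephone call and baseline visit, matching one to a known slot is harder than the arithmetic suggests. This stands.
- **It depends on which sentence is true.** Under simple randomization the share is zero. This also stands, although the block of 6 is the more specific statement.
- **Safeguards exist.** Independent custody is stated, and so is allocation after consent. A reader might infer that consent could follow allocation; the text rules that out. What stays open is narrower: Table 1 lists spot urine and blood after randomization. That may be only list order, since Study design puts allocation after the baseline evaluation.
- **Articles condense.** Operational detail on concealment may sit in the full protocol, so the absent explanation is not held against the plan. Condensation does not excuse two conflicting sentences.
- **Varying blocks is a partial remedy.** A reader might infer that it moves 68% towards 50%. It does not; only the certain share falls.
- **Bias is already acknowledged, and some adjustment is possible.** The limitations mention open-label bias, baseline DSRQ is measured, and covariance analysis is planned for the sodium change. That makes it too strong to say that no analysis could help. It does not address predictable allocation.

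**Conclusion.** The contradiction between blocked and simple allocation is certain and needs correction. If the fixed block of 6 is the scheme used, an unblinded recruiter who knows the block size and tracks the sequence could be certain of 25% of allocations on average, about 30 of 120. This assumes 3 + 3 blocks in one unstratified sequence and complete tracking.

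A reader might infer that a quarter of allocations were in fact known, or that the trial is biased. The documents do not support that: nothing shows that anyone exploited the pattern. The sample size is unaffected. The point is a worthwhile and inexpensive improvement in concealment, and for recruitment already done it can be reported and checked but not repaired.

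**What to change.** 1. State one scheme. Delete the reference to simple random sampling if the sequence is blocked.
2. For participants not yet randomised, have the independent list holder regenerate the sequence with randomly varying block sizes, for example 4, 6 and 8. Keep the sizes out of anything the recruiting team sees.
3. Because the best-guess rate stays near 68%, have the independent person release each allocation only after enrolment and all baseline measures are recorded, including spot urine and blood. Align Table 1 with this order.
4. For participants already allocated, report the scheme actually used and compare baseline characteristics between arms by position in block, in particular for allocations that were certain. With about 1.5 such allocations per block this check is weak: it can reveal a gross imbalance but cannot exclude steering.

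**Cost.** One re-run of the list, a text correction and a release step by someone already in place. If the change is made at the end of a block, the arms can differ by up to 4 should recruitment stop mid-block (half of a block of 8), against up to 3 now. The benefit is limited to those still to be randomised. The article does not give that number, and with recruitment open since November 2015 it may be small.

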### Control group

Participants allocated to the control group will attend a nutritionist consultation regarding general recommendations for hypertension, such as increasing their consumption of fruits and vegetables, reducing salt intake, avoiding processed food and high-sodium food, reducing body weight if Body Mass Index (BMI) >25 Kg.m^2^ and reducing their consumption of alcoholic beverages, and will be provided with an explanatory folder about hypertension. During 6 months, participants of the control group will have their blood pressure (BP), body weight and waist circumference measures assessed monthly. During the same period of time, participants will be also asked if they have any questions about food.

5th month	Preparation of low-sodium food: use of natural spices, salt substitutes (perceived behavioral control) End of intervention: review of items, motivation to sodium-restriction maintenance	
6th month	The end of follow-up evaluation: anthropometric assessment, blood pressure measurement and DSRQ application. Spot urine collection and blood collection	

*DSRQ* Dietary Sodium Restriction Questionnaire

The activities will be developed according to the instrumental subscales [23]:Attitude – explanation to understand the low-sodium dietary importanceSubjective norm – sessions about the influence of family and others in choices and food preparation. Family support in sodium-restriction-diet adherencePerceived control – learning sessions to increase information about food choices, cooking or preparing food without salt, evaluating recipes and making suggestions for changes to low-sodium food, learning to read labels (strategies to increase low-sodium diet adherence)Dependent behavior – learning sessions on the amount of sodium in food, including salt quantity demonstrations, low-sodium food selection, changes in food choices in restaurants, being aware of the need to change both taste and food preferences

### Study variables and methods of assessment

The research team will be responsible for the triage and selection of eligible participants, and three members of the team will obtain the written informed consent signatures prior to entering the study. Researchers will not be blinded to participant intervention. The investigators will be trained to perform anthropometric standardization and BP measurements as well as the application of questionnaires. A laboratory technician will collect both spot urine and blood collection after 12-h fasting and the samples will be forwarded for analysis.

#### Blood pressure (BP)

BP will be measured with the participant seated quietly, with feet on the floor and arm supported at heart level, according to guidelines [24]. The cuff size will be used according to arm circumference; two measurements will be taken and the average recorded. BP will be measured at all visits.

#### Anthropometric measurements

The anthropometric measurements to be collected will be body weight (BW), height, waist circumference (WC) (midpoint between the last rib and the superior edge of the iliac crest) and Body Mass Index (BMI) in all visits.

#### Blood collection

Blood collection will be analyzed after 12-h fasting at baseline and at the end of the follow-up for clinical assessment (total cholesterol, high-density lipoprotein (HDL)-cholesterol, low-density lipoprotein (LDL)-cholesterol, triglycerides, glucose, sodium and potassium).

#### Spot urine analysis

Spot urine will be collected to estimate sodium intake, at baseline, after 2 months and at the end of the follow-up (6 months).

#### 24-h ambulatory blood pressure monitoring (ABPM)

AMPB will be performed using Spacelabs 90207 devices (Redmond, WA, USA). The protocol includes BP measurements every 15 min during daytime (6:00 a.m. to 10:00 p.m.) and every 20 min during nighttime (10:00 p.m. to 6:00 a.m.). ABPM will be considered satisfactory if at least 16 valid readings during daytime and 8 valid readings during nighttime are obtained [25]. Participants will be evaluated by ABPM at the baseline and at the end of the follow-up (6 months) in order to register BP during both sleep and wakefulness.

#### Dietary Sodium Restriction Questionnaire (DSRQ)

The participants will answer the DSRQ for the assessment of sodium-restriction adherence at the baseline, 2 months and at the end of the follow-up. This application will guide the educational intervention.

#### Dietetic assessments

The participants will answer the 24-h dietary recall for monitoring low-sodium diet adherence, detailing of food and portion consumed, as well as the ingredients, including information on time, place and quantity.

